## Abstract

**Background:**

There is consensus that research participants should be informed about plans for return of genetic research results. However, best practices for return of results in large biobank and cohort studies do not exist currently, and how best to communicate actionable genetic research results remains unclear. While having genetic counselors disclose these results may be ideal to ensure understanding, minimize distress, and optimize medical follow-up, genetic counselor (GC) workforce shortages and costs are barriers. The RESPECT3 study evaluates whether digital delivery alternatives for pre-disclosure education and return of actionable genetic research results is non-inferior to remote telehealth disclosure by a genetic counselor.

**Methods:**

The RESPECT3 Study is a hybrid type 1 effectiveness-implementation study which evaluates digital alternatives for pre-disclosure education and return of actionable research results in randomized non-inferiority trial. The return of results process in RESPECT3 uses a two-step process. In step one, participants with an actionable result and procedural controls (no actionable result) are invited to digital pre-disclosure education and provided options for opting out of results. In Step 2, those with actionable results who have not opted out are randomized to receive results via a digital disclosure intervention (digital-ROR) or with a GC. Participants include English-speaking adults who enrolled in the Penn Medicine BioBank (PMBB) and have an actionable research result according to the ACMG secondary findings list. The primary outcomes are non-inferiority of knowledge and disease specific distress (cancer and cardiovascular disease) after receipt of research results. Uptake of research results is a secondary non-inferiority outcome. Confirmatory clinical testing is covered by the study and all participants with confirmed results are referred to the appropriate clinical genetic program for clinical recommendations.

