#### Randomization

After at least 4 weeks, participants with an actionable finding (cases) who have not chosen to opt-out of receiving their results are randomized to receive their results by remote telehealth disclosure with a GC (Arm 1) or by a private ROR digital intervention (Digital-ROR) with the option to schedule a call with a GC at any time in the process (Arm 2). A permuted block design is used for randomization, stratifying by cancer or cardiovascular genes and sex.

Randomized participants are sent the Step 2 Letter by MyPennMedicine portal (MPM), encrypted email or mail informing them that an actionable genetic finding that could potentially impact their health has been identified (Supplemental Fig. 2). The letter includes how they will receive their actionable results (according to their randomization), the next steps for receiving results and that they can still elect to NOT receive results. Procedural controls do not receive the Step 2 Letter, but any who opt-out of results after the Step 1 Letter has their decision recorded in case they are found to have an actionable result with additional sequencing or analysis.

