
#### Moderators of uptake and patient reported outcomes (aim 3a)

Moderators are collected at baseline and include sociodemographics, health literacy, comfort with technology and general health status. Sociodemographic data includes race/ethnicity, education, marital status, gender, age, zip code, health insurance status, usual source of care status, employment status, financial wellness [130] and household income. Test result, including cancer versus cardiovascular/other actionable result and the specific gene are recorded. General health status [129] and personal and family history of cancer and cardiovascular disease are included in the baseline survey. Health literacy is assessed at baseline (T0) with 3 items validated to detect inadequate health literacy in clinical medical populations [131]. Comfort with technology is assessed with selected items from the NCI Health Information National Trends Survey (HINTS), including internet and social media use electronic medical record use and perceptions of privacy (7 items) [132].

Additionally, individual use of digital interventions are recorded throughout the study to evaluate the impact of intervention usage (e.g. dosage) on outcomes and who benefit from supplemental digital education or digital-ROR.

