### Data analysis plan

#### Primary non-inferiority analyses

We hypothesize that disclosure of actionable results by digital-ROR, with access to a GC, can provide non-inferior short-term and longitudinal cognitive, affective, and behavioral outcomes, and lower costs. Primary effectiveness outcomes include: post-disclosure knowledge and cancer or cardio disease-specific distress. We will test whether the receipt of results differ between arms as a secondary analysis. Receipt of results is considered a health behavior. For the 2 primary analyses, we will apply non-inferiority tests to examine if access to digital-ROR is non-inferior to GC disclosure. We will conclude non-inferiority if the upper bound of the randomization effect 97.5% one-sided confidence interval [CI] for cross-sectional T1 responses do not cross a -0.45 standardized difference threshold (i.e., margin) for knowledge and a 0.2 standardized threshold (i.e., margin) for disease-specific distress in the direction that would suggest that digital-ROR is worse. A standardized difference is the difference after variables are scaled to have standard deviation (SD) one with respect to baseline SD. We based the margins on what might be considered clinically relevant effects given our pilot data. We will use intention-to-treat approaches, comparing randomized arms, with confirmation by per-protocol analyses (i.e. restricting sample to those who properly used the method of disclosure as assigned). We will only declare non-inferiority if both intention-to-treat and per-protocol analyses are consistent, as recommended [133, 134]. For the secondary outcome receipt of results, we will examine non-inferiority of proportions. We will declare non-inferiority if the upper bound of the randomization effect 95% one-sided confidence interval for receipt of results is < 10% in the direction that favors usual care. Since all participants will have the option to speak with a GC, we will conduct secondary as-treated analyses (i.e. based on whether genetic counseling was actually received in both arms).

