We chose *n* = 255/arm so we could conclude non-inferiority of digital-ROR if randomization effects comparing the digital arm to GC arms at T1 do not show clinically relevant worsening in the web arm. We chose a margin of -0.45 standard deviation units for knowledge and 0.20 for distress since they are considered modest changes in behavioral research, and they are consistent with our pilot data. In preliminary data from our pilot study, the baseline knowledge standard deviation was 2.86 points. A -0.45 standard deviation difference * (times) 2.86 = -1.29 points. A 1.29 point worsening in the knowledge scale would not be considered a meaningful difference. For disease specific distress, the baseline standard deviation was 9.31 points. A 0.20 standard deviation difference * (times) 9.31 = 1.86 points. Again, a 1.85 unit worsening in the distress scale would not indicate a clinically relevant change.

Table 4 demonstrates potential allowable non-inferiority differences. We chose 2.5% Type I error by applying a Bonferroni correction to a 5% Type I error rate with 2 comparisons (5%/2 = 2.5%). We calculated power using simulations in R with confirmation using PASS 11 software. For our secondary outcome of receipt of results, we will declare digital-ROR effect non-inferior if the upper bound of the 95% one-sided confidence interval effect is less than 11% in a direction that would favor usual care. This has an approximate 5% non-inferiority Type I error rate and > 80% power over a range of plausible differences given our preliminary data (e.g. >55% promising rate seen in preliminary data versus < 44% discouraging rate, *n* = 255/arm). We assumed a binomial pooled standard error estimator. We do not correct for multiple testing of secondary outcomes.

**Table 4 Tab4:** Estimated non-inferiority power, 2.5% Type I error (1-sided), number = 255/group (510 total)

Variable	Biobank Wave 2 Pilot Study	Non-inferiority difference allowed	Non-Inferiority Type 1 Error Rate and Power
Knowledge	T1 Mean 13.20, SD = 2.59 GC arm T1 Mean 12.50, SD = 2.12 Web arm Web minus GC effect = -0.7 Baseline standard deviation = 2.86	-0.45 SD units * 2.86 base SD = -1.29 point margin	2.5% Type I error rate > 80% power with − 0.7 pilot data effect > 99% power with 0 point effect

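### The non-inferiority test for receipt of results is unadjusted, although education use before randomisation is logged and could be pre-specified as a covariate (optional gain in precision, size unknown)

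*Protocol article*

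**What the plan says.** The abstract of the Protocol article sets the status of the outcome: "Uptake of research results is a secondary non-inferiority outcome". Under Primary non-inferiority analyses, the method for receipt is given in one line: "For the secondary outcome receipt of results, we will examine non-inferiority of proportions". The decision rule follows: "We will declare non-inferiority if the upper bound of the randomization effect 95% one-sided confidence interval for receipt of results is < 10" per cent, in the direction favouring usual care. No covariate is named for this test.

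The next paragraph of the data analysis plan covers secondary analyses. It names logistic regression for behaviours, with receipt of results as an example, to adjust for potential confounders that turn out to be inadequately balanced.

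Sample size justification for aim 1 gives a different limit, "upper bound of the 95% one-sided confidence interval effect is less than 11% in a direction that would favor usual care", and says of it: "This has an approximate 5% non-inferiority Type I error rate". It claims more than 80% power at 255 per arm, with 55% as the promising rate and 44% as the discouraging rate, and adds: "We assumed a binomial pooled standard error estimator".

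On timing, the Step 1 letter carries links to the web education and Chat 1. Randomisation comes later: "After at least 4 weeks, participants with an actionable finding (cases) who have not chosen to opt-out of receiving their results are randomized". Blocks are stratified by gene group (cancer or cardiovascular) and sex. Under the Aim 3a moderators, "individual use of digital interventions are recorded throughout the study to evaluate the impact of intervention usage". The Aim 2 analyses already classify education as accessed or completed. Ethics approval requires new consent only for the surveys.

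**The concern.** Each case has at least four weeks between the Step 1 letter and randomisation in which to open the education, and that use is recorded individually. People who engage with a first notice may be more likely to act on a second. If so, education use before randomisation carries information about receipt that the margin test does not use. Unlike the baseline survey measures, it should be available for every randomised case, because non-use is itself a value.

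The planned secondary regression does not fill this gap. It is triggered by observed imbalance rather than by prognostic value. Its natural output is an odds ratio, which cannot be set against a limit in percentage points. It also does not require the stratification factors.

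At stake is the width of the confidence bound for the one secondary outcome that has its own non-inferiority limit and power statement.

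**Working it through.** **Inputs from the article.** 255 per arm; one-sided 5%; 55% receipt, taken as equal in both arms; limits of 11 points (sample-size section) and 10 points (analysis section).

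**Reproducing the stated power.** Pooled SE = sqrt(2 × 0.55 × 0.45 / 255) = 0.0441. Power = Phi(limit / SE − 1.645).

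- 11 points: Phi(2.497 − 1.645) = 80.3%. Eighty per cent power needs 253 per arm, so the stated figure is reproduced with almost nothing over.
- 10 points: Phi(2.270 − 1.645) = 73.4%. Eighty per cent power would need 307 per arm.
- With a true deficit of 2 points in the digital arm, power is 65.3% (11 points) or 56.7% (10 points).

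**Effect of adjustment.** For a yes/no covariate with prevalence q and a difference d in receipt between users and non-users, the share of variance explained is R² = q(1 − q)d² / (0.55 × 0.45), and the SE is multiplied by sqrt(1 − R²). The article gives neither q nor d. The table assumes q = 0.30 and varies d; the last column is 255 / (1 − R²).

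| Assumed gap d | R² | Power, 11 points | Power, 10 points | Equivalent unadjusted n per arm |
|---|---|---|---|---|
| 0 | 0 | 80.3% | 73.4% | 255 |
| 20 points | 0.034 | 81.5% | 74.7% | 264 |
| 30 points | 0.076 | 83.0% | 76.3% | 276 |
| 40 points | 0.136 | 85.1% | 78.7% | 295 |
| 50 points | 0.212 | 87.9% | 81.9% | 324 |

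Across R² of 0.034 to 0.212 the gain is 1.2 to 7.6 points of power at the 11-point limit and 1.3 to 8.5 at the 10-point limit. R² of about 0.17 is needed to bring the 10-point test to 80%.

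**Simulation check.** With 8,000 trials per setting, a linear covariate-adjusted risk difference, 40% prior use and gaps of 20, 30 and 40 points, power at 11 points went from 80.4% to 81.7%, 80.3% to 83.4%, and 79.4% to 85.4%. Type I error of the adjusted test was 4.5% to 5.2%.

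**Validity of the covariate.** The two disclosure-arm sections direct people who have not done the education to complete or decline it after randomisation. Only use dated before randomisation is therefore unaffected by arm.

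**The case against.** An unadjusted comparison of randomised proportions is standard and unbiased, and covariate sets are often left to a statistical analysis plan, which is not shown here. That stands: nothing in the stated test is invalid, and this is a matter of efficiency only.

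Four stronger readings are tempting, and the article does not support them.

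- *That the final analysis will use a pooled standard error.* The pooled estimator is stated as an assumption of the power calculation. The analysis section fixes no variance estimator.
- *That adjustment of receipt was overlooked.* The secondary logistic regressions name receipt and could correct a chance imbalance in prior engagement. They do not, however, feed the test against the limit.
- *That education use is a strong predictor of receipt.* No association is reported. Education can still be completed or declined after randomisation, and non-responders in both arms are pursued by phone, email, letter and Chat 2; both could weaken it. With 20% prior use and a 20-point gap, R² is 0.026 and power is 81.2% (11 points) or 74.4% (10 points), a gain of about one point.
- *That power is bound to be short.* This depends on 255 per arm being the receipt denominator. The knowledge calculation in Table 4 needs 255 T1 scores per arm: SE = sqrt((2.59² + 2.12²) / 255) = 0.210, and Phi((1.29 − 0.70) / 0.210 − 1.96) is about 80%. The interim analysis was also counted by completed T1 surveys. If 255 means T1 completers, more people are randomised. Purely as illustration, 255 / 0.55 = 464 per arm would give unadjusted power of about 96% (11 points) or 92% (10 points). The sample-size section does state 255 per arm for receipt, so the article leaves this open.

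**Conclusion.** The point holds as a low-severity, optional improvement. The margin test for receipt is unadjusted, and the planned adjustment is imbalance-triggered and on a different scale. A usable baseline covariate is logged without survey consent. That it is complete for all randomised cases is inferred from individual logging, not stated.

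The gain is about 1 to 8 points of power for R² of 0.03 to 0.21, at 255 per arm and 55% receipt in both arms. The R² range is an assumption; with no association the gain is nil and essentially nothing is lost. A reader might infer that the receipt test is invalid or clearly underpowered. Neither follows: the first is contradicted by randomisation, and the second turns on the denominator and on which limit applies.

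The conflict between the 10-point and 11-point limits is a separate inconsistency, worth about 7 points of power (80.3% against 73.4%), and must be reconciled in its own right. Adjustment does not resolve it.

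**What to change.** Before the final analysis, pre-specify the receipt analysis as a standardised risk difference. Use a logistic working model with arm, education status before the randomisation date (none, accessed or completed; web or Chat 1), gene group and sex. Use a robust or bootstrap standard error and compare the one-sided 95% bound with the single reconciled limit. Exclude any education use dated on or after randomisation. Keep the raw-proportion test as a supporting analysis, and state the receipt denominator.

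The cost is some analysis-plan wording and a merge of existing usage logs with randomisation dates; no new data or recruitment is needed. There are two small downsides. The main estimate becomes model-assisted. The usage logs must also be checked for continuity, because the chatbots moved from an external vendor to an internal platform in 2024.

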**Discussion:**

The RESPECT3 study is expected to provide critical empiric data on the effectiveness of using digital alternatives for pre-disclosure education and return of genetic research results in a representative clinical population of research participants who enrolled in an institutional biobank where return of results was not the focus of the study. Equally important, our theoretically-informed process evaluation data is expected to inform modifications to identify barriers and facilitators to broader implementation.

**Trial registration:**

NCT04242667.

**Supplementary Information:**

The online version contains supplementary material available at 10.1186/s12910-026-01439-x.

## Background

Large prospective cohort studies that have banked DNA are using advance genetic sequencing to better understand the effects and interplay of genes, the environment and lifestyle on health outcomes [1, 2]. The hope for personalized medicine is to tailor prevention, treatment or screening recommendations for individual patients based on their genotype or other genomic profiles, which will ultimately result in modified health behaviors (e.g. risk reducing behaviors or screening) and improved patient outcomes [3–5]. However, genetic sequencing can identify actionable genetic variants that are likely to have medical impact on the research participants and their families.

The potential to incidentally identify “actionable” genetic variants (i.e. those that are likely to have a medical impact and are amenable to medical intervention or screening) has raised questions regarding obligations to share such findings with research participants and how it should be shared [2, 6–11]. Several studies suggest that many research participants are interested in receiving at least some genetic research results [12–19]. Based on principles of autonomy and respect for persons [14, 15, 20–26], there is consensus that research participants should be informed about the return of genetic research results, including the type of results, the process, and the option to decline [6, 8, 27–34]. However, best practices for implementation of these recommendations in large biobank and cohort studies do not exist currently. Most programs send participants a letter outlining a plan to return results and the option to “opt-out” [35–37], which may not suffice for well-informed decision making, particularly when details at consent were limited and the ACMG actionable results list covers a range of cancers, cardiovascular and other medical conditions [35, 38–41]. Pre-test counseling by genetic counselor (GCs) is a standard that could be applied to ensure informed decision making (e.g. advantages). However, this approach is costly and impractical for research programs and alternative cost-effective strategies are needed [42]. 

Similarly, how best to communicate genetic research results to research participants remains unclear. Unlike patients with clinical genetic testing, research participants may not be prepared for actionable results, particularly if the results are unrelated to the reason they enrolled in research, or if they enrolled as healthy unselected participants many years prior (e.g. large biobanks). While having GCs disclose these results may be ideal to ensure understanding, minimize psychosocial distress, and optimize medical follow-up and cascade testing [43], GC workforce shortages and costs are barriers [43, 44]. Many programs have used GCs to share genetic research results [8, 35, 37, 45–47], while others have provide results to local health care providers [48, 49] who may lack the necessary expertise or resources, resulting in suboptimal patient outcomes [50]. Interactive patient-centered digital interventions and/or videos developed by genetic providers may provide a cost-effective alternative [51–54]. Further, these interventions could be paired with genetic counseling for participants with remaining questions, while still reducing overall provider time. Potential disadvantages include poor understanding, increased test-related short-term and/or long-term affective responses or suboptimal post-test behaviors (e.g. medical management and cascade testing). Limited data exist on patient outcomes, clinical outcomes, and costs associated with various approaches. Empirical data are needed to inform best approaches for pre-disclosure education and returning results to realize benefits for participants.

Although research participants have reported high interest in receiving research results [15, 48, 55–62], uptake has been lower when results have been offered (48–86%), particularly in biobank studies where return of results was not emphasized during enrollment and uptake has generally been around 50% [36, 38, 63–69]. There are limited patient-reported outcomes in research settings [63–65, 70], although some genomic implementation studies report no psychological harms with return of genetic findings [71, 72]. In the RESPECT2 study, research participants could choose pre-disclosure education with a GC or a patient-centered digital intervention. All participants received results with a GC. Favorable cognitive (e.g. knowledge) and affective (e.g. distress and uncertainty) responses were found, although the number of actionable results was small [73, 74]. 

### Objectives

The goal of the RESPECT3 Study is to conduct a Hybrid Type 1 effectiveness-implementation study to evaluate digital delivery alternatives for pre-disclosure education and return of actionable genetic research results. Based on our preliminary data and related research, we include both digital pre-disclosure education interventions and a private web-based portal for return of individual research results as an alternative to result disclosure by a genetic provider. Additionally, the study incorporates three chatbots designed to increase completion of pre-disclosure education, receipt of results and clinical confirmation testing.

#### Specific aim 1

Our primary aim is to evaluate in a randomized study whether disclosure of actionable genetic results by a digital intervention (digital-ROR) provides non-inferior short-term and longitudinal outcomes (knowledge, psychological distress, health and psychosocial behaviors and costs) compared to remote telehealth disclosure by a genetic counselor (GC)(e.g. usual care).

#### Specific aim 2

Our secondary aims are to evaluate the uptake of supplemental digital education (offered through a digital intervention or a chatbot) among Penn Biobank research participants notified of the option to opt-out of receipt of actionable genetic research results (Aim 2a), to evaluate the frequency of opting-out of receipt of actionable genetic research results (Aim 2b) and to evaluate the impact of use of digital education on opting out of receipt of actionable results (Aim 2c).

#### Specific aim 3

Our third aim is to conduct a multi-stakeholder mixed-methods process evaluation to understand the potential moderators (e.g. intervention usage, sociodemographic factors, genetic test result) of short-term and longitudinal outcomes to understand who benefits more or less from digital education and digital return of results (Aim 3a), and to understand the facilitators and barriers to implementation of digital interventions for return of actionable genetic research results and recommendations for future adaptation and sustainability (Aim 3b).

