#### Aim 3 analyses

We hypothesize that moderators will identify those who benefit more and less from the eHealth interventions and can inform policies for return of results. For moderation (i.e., effect modifiers), we will include in regressions described in Aim 1 an indicator variable for randomization arm, panel time indicators (for longitudinal models examining all three time points), the potential moderator variable, and all two-way and relevant three-way interactions among the arm/time/moderator variables [135]. To maintain power, we will examine non-time moderators separately.

Qualitative data will be analyzed using an iterative, deductive content analysis approach and CFIR as the coding framework [107, 110, 137]. The qualitative data will include: (a) participant surveys and key informant interviews; (b) notes and debriefing from our research team meetings. Guided by consensual qualitative methods [138, 139], two independent coders will review notes and assign responses to CFIR constructs. Using a convergent mixed-methods approach [140], we will merge quantitative and qualitative data, organized by the 5 CFIR domains to evaluate which constructs were associated with, or more prevalent among: (a) patients who used the digital interventions exclusively versus those who used digital interventions and requested a GC versus those who requested to speak with a GC and declined use of digital interventions, (b) participants who used chatbot options versus web-based options, (c) participants who had confirmation testing and clinical medical follow-up versus those who did not, and (d) those who shared results with multiple relatives versus those who did not, providing an opportunity to comprehensively evaluate facilitators and barriers to implementation of digital alternatives for return of actionable genetic research results in large biobanks and research cohorts. We will use descriptive statistics, correlations, and generalized linear models, assuming appropriate link and family functions, to examine quantitative variables associated with barriers and uptake. We will estimate longitudinal models by Generalized Estimating Equations.

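### Aim 3a lists intervention usage as a moderator, but an arm-by-usage interaction cannot be estimated for digital-ROR use and may be biased for other usage that arises after randomisation

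*Protocol article*

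**What the plan says.** Three sections of the protocol article bear on this.

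- *Objectives, Specific aim 3* gives as examples "potential moderators (e.g. intervention usage, sociodemographic factors, genetic test result", and states the purpose as "to understand who benefits more or less from digital education and digital return of results (Aim 3a".
- *Moderators of uptake and patient reported outcomes (aim 3a)* opens with "Moderators are collected at baseline and include sociodemographics, health literacy, comfort with technology and general health status". A separate paragraph under the same heading adds that "individual use of digital interventions are recorded throughout the study to evaluate the impact of intervention usage (e.g. dosage) on outcomes".
- *Aim 3 analyses* treats moderators as effect modifiers: "For moderation (i.e., effect modifiers), we will include in regressions described in Aim 1 an indicator variable for randomization arm". Time indicators and the moderator follow, with "all two-way and relevant three-way interactions among the arm/time/moderator variables". Moderators other than time are examined one at a time. Usage is not handled differently.

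Two facts about the design decide what this model can estimate. Digital-ROR is the disclosure route of Arm 2; the outcomes section counts viewing results there as uptake for the digital arm only. The education website and Chat 1 are offered to all cases in the Step 1 letter, at least 4 weeks before randomisation. Under the Arm 1 and Arm 2 headings, those who have not completed education are again directed to complete or decline it after randomisation.

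**The concern.** An effect modifier is a characteristic across whose levels the arm effect is compared. That requires people from both arms at each level, and a level that the arm did not itself produce. Usage of digital-ROR fails the first condition, because nobody in the GC arm has any. Usage that arises after randomisation can fail the second, because the arm may influence who engages.

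Aim 3a is meant to say who gains from the digital tools, and Aim 3 analyses expects the moderators to inform return-of-results policy. A dose association produced by this model could be read as evidence that people who use the portal more gain more from being assigned to it. It may only show that engaged, more literate or more technically confident people both use it more and score better.

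**Working it through.** No figure in the protocol relates to this point: there is no sample size, power or effect size for Aim 3. The check is therefore structural, followed by an illustration whose inputs are assumed.

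**1. Digital-ROR usage, cross-sectional model.** Let A = 0 for GC and 1 for digital, and U = digital-ROR usage. The model is

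Y = b0 + b1·A + b2·U + b3·(A×U).

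In the GC arm U = 0, so A×U = 0 = U. In the digital arm A = 1, so A×U = U. The columns A×U and U are identical for every participant. With 255 per arm (Enrollment goals), the design matrix has rank 3 for 4 columns. Only b2 + b3 can be estimated, not b3.

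**2. Digital-ROR usage, three time points.** The columns are 1, A, U, A×U, two time indicators, and the products of A, U and A×U with each indicator: 4 + 2 + 6 = 12. A×U and its two time products duplicate U and its two time products, so the rank is 12 − 3 = 9. The computed rank is 9. This result needs no assumption about effect sizes.

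**3. What is left.** If software drops the duplicate column, the remaining coefficient compares Arm 2 users with Arm 2 non-users. Usage is self-selected. Because moderators are examined separately, health literacy and technology comfort need not be in the usage model. The Aim 1 adjustment covers only confounders imbalanced between arms, which is a different matter from predictors of engagement.

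**4. Illustration of the selection.** Assume no arm effect and no effect modification. An unmeasured trait L, standard normal, correlates r with an outcome of SD 1. A participant is a user when L plus independent standard normal noise exceeds zero. The correlation of L with that sum is 1/√2 = 0.7071. The expected user-minus-non-user difference is

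r × 2 × 0.7071 × √(2/π) = r × 2 × 0.7071 × 0.7979 = 1.128·r.

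| assumed r | spurious difference (SD) |
|---|---|
| 0.1 | 0.11 |
| 0.3 | 0.34 |
| 0.5 | 0.56 |

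A simulation of 2,000 trials at r = 0.5 gave 0.57 SD, significant in 99.6% of runs.

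**5. Usage in both arms after randomisation.** This model has full rank. In an extreme case, usage depends on L in the digital arm and is pure chance in the GC arm. At r = 0.5, simulation with no true modification gave an interaction of 0.56 SD, significant in 90% of runs.

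**6. Education use before randomisation.** Full rank, 4 of 4. With the same trait driving use equally in both arms, the simulated interaction was −0.002, significant in 6% of runs, close to the nominal 5%. This variable behaves as a moderator should.

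The values of r are assumptions; the protocol reports no association between engagement and outcome. Steps 4 and 5 show a mechanism and do not estimate bias in this trial.

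**The case against.** The strongest reply is that no arm-by-usage model is written down. Aim 3 analyses does not name usage, and it appears as a moderator only as an example in the objectives. The Aim 3a moderator section sets it apart from the baseline variables as a dosage question. A reader might therefore say that the protocol plans no such interaction, or conversely that it plans one explicitly. Neither is supported. The model follows from reading the objectives with the single moderation formula, which exempts nothing. The dosage paragraph stands under the moderator heading and also speaks of who benefits.

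A reader might also infer that all intervention usage arises after randomisation. That is wrong: the Step 1 letter gives every case access to education at least 4 weeks earlier, and use in that window is a legitimate moderator.

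Nor does the moderator section flatly contradict the objectives. The objectives do not say when moderators are measured, and the moderator section adds usage separately. This is loose wording that needs reconciling.

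Finally, software would flag the duplicate column, and the surviving contrast is the within-Arm-2 comparison recommended below. That stands, but it does not settle how the contrast would be labelled or adjusted. An unseen analysis plan may define the usage measures; the point here concerns a stated moderator paired with a stated model.

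**Conclusion.** The point holds in limited form. For digital-ROR usage the arm-by-usage interaction is not identified. This rests on one premise, that GC-arm participants have no digital-ROR use, which the protocol's definition of uptake supports. For education completed after randomisation, the interaction can be estimated but may be biased, by an amount that cannot be calculated from the protocol. For education use before randomisation there is no objection.

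The consequence is confined to Aim 3a. It would be an overreach to infer any damage to the primary comparisons of knowledge and distress or to the secondary comparison of receipt of results, since none of these uses usage as a moderator.

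**What to change.** - Reconcile the objectives, the Aim 3a moderator section and Aim 3 analyses, so that a moderator in the arm-by-moderator models means a variable fixed before randomisation.
- Include education use (website or Chat 1) up to the randomisation date among these, where usage logs can be dated.
- Remove digital-ROR usage and any other usage after randomisation from those models.
- Report digital-ROR usage within Arm 2 only, adjusted for baseline health literacy, comfort with technology and T0 scores, and label it an exploratory association.

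The cost is mainly wording, because usage and the adjustment variables are already collected. One thing needs checking: the protocol says that use is recorded throughout the study but does not say that records carry dates. If they do not, education use cannot be split at randomisation and should also leave the interaction models. The scientific price is small: no usage-based statement about who benefits can be made for digital-ROR, which the planned model could not have supported anyway.
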